### Aims of This Study

This paper describes the protocol for a study that will test the effectiveness of an intervention using a mobile city game, Safe City, to improve the safety knowledge and behaviors of Hong Kong Chinese children in Grades 4-6 by a randomized controlled trial. Our hypotheses are as follows: (1) children in the intervention group (ie, those who receive the Safe City game intervention) will have higher levels of correct safety knowledge and behaviors than children in the control group (ie, those who receive electronic and printed safety information) at 1- and 3-month follow-ups. (2) We expect a change in the children’s functioning and psychosocial difficulties. At 1- and 3-month follow-ups, we expect that children in the Safe City intervention group will show better functions and fewer psychosocial difficulties than those in the control group. (3) We expect that those who play the game more frequently will show greater improvement in safety- and health-related outcomes.

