### Game Design

The mobile game, Safe City, will be co-designed by our project team (pediatricians, psychologists, safety experts, and experienced health promotion researchers) and the game development team (programmers, artists, and sound designers). The model of learning used in the Safe City game will be guided by the social cognitive theory [25] and elaboration likelihood model [26]. The elaboration likelihood model proposes that capturing attention is the first step in motivating people to process information [26], whereas the social cognitive theory proposes that behavioral change is a function of improved skills and confidence through repeated modeling, feedback, or both [25]. Hence, the Safe City game will be packaged as an RPG with multiple components to teach players how to recognize and minimize injury hazards to prevent injuries in a real-world environment.

In the game, players will start by indicating their preferred gender, hairstyle, facial features, and clothing for their human avatar who will assume the role of safety inspector in the virtual city. This avatar-creation approach is to engage the player in the game as if he or she is exploring the game city using the first-person perspective. As a safety inspector, the player will use the city map provided in the game to identify safe routes to navigate between potentially dangerous checkpoints (homes and athletic areas) and assess the safety level of the checkpoints in the busy and lively land of Safe City. The gameplay will feature mini games (eg, multiple choice questions, spot the danger, and matching items to reinforce safety messages) with fun elements such as game points and in-game ranking to encourage daily play of the game plus engagement strategies such as positive reinforcement (ie, point addition for each correct response) and response cost (ie, point deduction for each incorrect response) to promote safety behavior.

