### Data Analysis

Results will be reported from intention-to-treat analysis, where outcome variables of the dropouts will be assumed to be unchanged from the previous assessments to provide a conservative estimate. A complete-case scenario will also be considered as a sensitivity analysis. The effectiveness of the intervention in achieving the proposed targets will be estimated using linear mixed models. Group allocation will be included as dummy independent variable. School will be controlled as random intercepts, whereas covariates, such as child’s age and sex and family socioeconomic status, will be adjusted as fixed independent variables. The linear model will be used for continuous outcomes, whereas logistic and Poisson models will be used for binary and count variables, respectively. The association between total game points and pre–post changes in outcomes will also be analyzed using the linear mixed models among students in the intervention group. Students in the control group will not be considered in this analysis because they will not be able to access the game. Game usage statistics will be added to the model as independent variables.

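### In the within-arm game-use analysis the carry-forward rule is not conservative: game-arm children with no follow-up enter as zero change, which can tilt the slope towards hypothesis 3

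*Protocol article*

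**What the plan says.** All the relevant rules stand in one paragraph of the protocol article, under Data Analysis.

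- **Scope.** It opens with "Results will be reported from intention-to-treat analysis" and attaches the dropout rule to that: "outcome variables of the dropouts will be assumed to be unchanged from the previous assessments to provide a conservative estimate". No analysis is exempted.
- **Sensitivity analysis.** The next sentence reads: "A complete-case scenario will also be considered as a sensitivity analysis".
- **Game-use analysis.** Later in the paragraph: "The association between total game points and pre–post changes in outcomes will also be analyzed using the linear mixed models among students in the intervention" arm. Usage statistics enter as independent variables. No separate missing-data rule is given.

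The hypothesis served is the third under Aims of This Study: "We expect that those who play the game more frequently will show greater improvement in safety- and health-related outcomes". Game Design describes "point addition for each correct response" and a deduction for wrong answers. Under Intervention, play is unlimited over four weeks. Outcomes are measured at baseline, 1 month and 3 months.

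**The concern.** Carrying a value forward is usually defended as pulling a between-arm difference towards zero. That defence does not transfer to a regression of change on use inside one arm. Here the outcome is itself the change, and no comparison arm receives the same imputation. A child with only a baseline assessment is given a change of zero, whatever really happened.

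Where these zeros fall along the points axis decides what they do. Points build up through voluntary play, so a child who disengages before the 1-month visit has plausibly collected fewer of them. The zeros would then gather at the low-use end, while the other children improve for any reason, such as retesting, maturation, or the game at any amount of play. The fitted slope rises with use even if use makes no difference. That is the direction hypothesis 3 predicts, so an imputation artefact could be reported as more play giving more benefit.

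**Working it through.** **The plan's own figure.** The only design figure is 80% power with 504 per group for d = 0.181. Check: 0.181 × √(504/2) = 2.873; 2.873 − 1.96 = 0.913; Φ(0.913) = 0.82, two-sided. It is reproduced. The point below uses only the 504.

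**Inputs from the document.** 504 children in the game arm, the carry-forward rule, and the regression of change on points.

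**Inputs assumed.** Dropout rate, its timing, the mean change in the arm, and how far leavers' points fall below stayers'. The document gives none of these, so ranges are used.

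**Step 1: the bias.** Let change (in the direction of improvement) have mean m and SD 1 and be independent of points and of leaving, so the true slope is 0. Let a fraction p have no follow-up and be set to 0. Let Δ be stayers' minus leavers' mean points, in SDs of points. The covariance of points with the imputed change is m times the covariance of points with staying, so

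slope per SD of points = m × p × (1 − p) × Δ.

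This is positive when m and Δ are both positive, and zero if either is zero.

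**Step 2: one case by hand.** Take m = 0.5, p = 0.20, and odds of leaving that double per SD fewer points. The simulated slope is 0.052, which implies Δ = 0.052 / (0.5 × 0.2 × 0.8) = 0.65.

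- Variance of imputed change: 0.8 × (1 + 0.25) − (0.8 × 0.5)² = 1.00 − 0.16 = 0.84.
- Standard error: √(0.84/504) = 0.0408.
- z = 0.052 / 0.0408 = 1.27.
- Two-sided rejection: Φ(1.27 − 1.96) + Φ(−1.27 − 1.96) ≈ 0.25, against 23.6% in the simulation.

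**Step 3: simulated false-positive rates.** True slope 0, nominal 5%, simple regression without school intercepts or covariates.

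*Mechanism A: odds ratio 2 of leaving per SD fewer points, 2000 runs per setting.*

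| Mean change | Timing | 10% dropout | 20% | 30% |
|---|---|---|---|---|
| 0.181 SD | all before month 1 | 5.4% | 6.6% | 9.6% |
| 0.3 SD | all before month 1 | 6.2% | 11.4% | 18.2% |
| 0.5 SD | all before month 1 | 9.8% | 23.6% | 40.9% |
| 0.3 SD | half after month 1 | 5.4% | 6.9% | 8.1% |
| 0.5 SD | half after month 1 | 6.9% | 9.1% | 12.0% |

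*Mechanism B: leavers at 25% of stayers' points, gamma-distributed points.*

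| Mean change | Timing | 10% dropout | 15% | 20% |
|---|---|---|---|---|
| 0.3 SD | all before month 1 | about 10% | 17% | 25% |
| 0.5 SD | all before month 1 | about 21% | 38% | 55% |

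With half of the leavers going after month 1, mechanism B gives about 7–9% at 0.3 SD and about 8–17% at 0.5 SD over the same dropout range.

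**Step 4: where it vanishes.** Under mechanism A, rates are 3.6–5.2% with mean change 0, 4.0–5.8% with dropout unrelated to points, and 4.9% when everyone leaves after month 1. Observed values alone give 4–6% throughout. That last result depends on the set-up, in which dropout is unrelated to change.

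**The case against.** A reader might infer that every leaver receives a zero, that leavers are known to be low scorers, and that the test of hypothesis 3 is therefore bound to mislead. The document does not support that.

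- **The zero is limited.** Only children with no follow-up get it. A child seen at month 1 carries that value, and the inflation falls sharply when many leave late.
- **The link to low use is inferred.** Nothing says who leaves, how many or when. Points are also deducted for errors. Usage is logged by the account system, so a child can play and still not return a questionnaire.
- **A complete-case analysis is named.** If the carry-forward sentence covers the game-use model, so arguably does the next one, and a gap between the two results would expose the artefact. Even so, complete case is only to be considered, is not expressly extended to this model, and would leave the carried-forward slope as the main result.
- **Scope can be read more narrowly.** Intention-to-treat is a term for comparing randomised groups, and the sponsor may have meant only those. The wording covers results without exception, so the wide reading is the literal one but not the only one.
- **An analysis plan not shown may settle this.** It may. The point rests on a rule that the article states and justifies as conservative, not on missing detail.

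These arguments limit size and priority. They do not make the stated justification correct for this analysis.

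**Conclusion.** The concern holds in limited form. As worded, the carry-forward rule reaches the within-arm analysis of change on game points, and there it is not conservative. The upward bias needs three things together: children with no follow-up, lower use among them, and average improvement in the arm.

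Under the assumed inputs of mechanism B, the false-positive rate is about 10–55% if all leave before month 1 and about 7–17% if half do. A milder link between use and leaving gives less, and at low dropout or small mean change the effect is slight. These figures show what the rule can do; they do not forecast this trial.

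Priority is minor to moderate. The analysis is secondary and non-randomised, and the between-arm comparison is unaffected.

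**What to change.** Add one sentence to the analysis plan: the main game-use analysis uses observed follow-up values, or a likelihood-based mixed model on the observed repeated measures, with no carried-forward values. Beside it, report game usage for children with and without follow-up data, so that readers can see whether leavers did play less.

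The cost is somewhat fewer children in this analysis. The result would still assume that dropout is unrelated to change given use and covariates, and this should be said. Adjusting for the baseline score is optional and does not address this defect. If carry-forward was meant only for the comparison of randomised groups, saying so removes the ambiguity, and the rule for the game-use analysis then needs to be stated.

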### Ethical Issues

This trial is registered on the ClinicalTrials.gov database (NCT04096196) and has been approved by the Institutional Review Board of Hong Kong University and Hospital Authority Hong Kong West Cluster (Reference number: UW 19-028).

## Results

Safe City is currently at the initial stages of development and programming of its prototype version. Acceptability and usability tests on target participants will subsequently be conducted to detect and correct occasional bugs or problems and refine the design. Participant recruitment will commence in September 2020. Completion of data collection is anticipated to occur in March 2021, and analysis of results will be undertaken by December 2021.

## Discussion

Childhood injury is a major public health problem. Although it is the leading cause of disability and death for children in many parts of the world [1,2], prevention strategies to tackle this public health problem are still inadequate. Health education is an important part of health promotion, and middle childhood is the ideal time for health education. In Hong Kong, safety training and programs often take place in formal education settings such as classroom. Although simulated road facilities such as Road Safety Town and Bus are available in the local community for children to learn road safety, this type of community-based learning has limitations such as short visit time and inconvenient location. Recent advances in technology allow students to learn with more opportunities to explore real-world problems and challenges in a virtual environment [9]. Evidence suggests that game-based learning may enhance positive learner experiences, feelings of empowerment and self-efficacy, and positive psychological outcomes including enjoyment and confidence [12,35,36]. Several safety games have been developed for Western children with high usage and download rates [9,23]. This will be the first report of a safety promotion game developed for Hong Kong child population. We are hopeful that the game can be a valuable tool for prevention of childhood injury in the community in the long run. Moreover, the resulting city game platform can be used for general health education purpose, so other health topics such as mental health and substance use can also be incorporated into the game in future development phases. Moreover, this is the first known research trial assessing the effectiveness of a mobile serious game in teaching children about safety knowledge and behaviors. Findings from this study will be made available to the public, local schools, news media, education groups, and safety organizations working to improve injury prevention in Hong Kong and beyond, as they could inform future innovative strategies for injury prevention.

## Appendix

Multimedia Appendix 1 Peer-reviewed reports of the funding agency.

## Abbreviations

RPG: role-playing game
VR: virtual reality
